## **2. Trial Objectives**

The purpose of this trial is to analyze intensity of fatigue in early-stage breast cancer treated with WBI or APBI after BCS. We propose that patients treated with APBI have lower fatigue levels after radiotherapy based on the FACIT Fatigue Assessment Questionnaire compared with patients treated with standard WBI.

### **2.1 Primary Objective**

The primary objective is the assessment of fatigue from baseline (before treatment start) compared to 12 weeks after treatment start as assessed by the FACIT Fatigue Assessment Questionnaire.

### **2.2 Secondary Objectives**

fatigue 5 weeks, 6 months, 2 years, 5 years after treatment start

local tumor control in the index quadrant of the breast after 2 and 5 years

local tumor control in the ipsilateral breast after 2 and 5 years

regional tumor control after 2 and 5 years

distant tumor control after 2 and 5 years

overall survival after 2 and 5 years

disease-free survival after 2 and 5 years

secondary malignancies after 2 and 5 years

acute and chronic toxicity after 5 weeks, 12 weeks, 6 months, 2 years, 5 years after treatment start

quality of life 5 weeks, 12 weeks, 6 months, 2 years, 5 years after treatment start

cosmesis 5 weeks, 12 weeks, 2 years, 5 years after treatment start

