### 6.4 Study visits

After screening of patients for inclusion and exclusion criteria and having received informed consent, appropriate patients will be recruited to the trial. Study relevant data will be collected and patient history will be assessed. Patients will be randomized 1:1 to one of the two study arms. The baseline visit (To) will be scheduled -7 to -1 day before planned treatment start. During the baseline visit (To) a clinical assessment as well as analysis of cosmesis and quality of life including fatigue is planned (and FACIT Fatigue Assessment Questionnaires, see 6.4). Patients will also receive photographic documentation for cosmetic assessment.

Patients in arm A are treated with BCS followed by hypofractionated WBI with a total dose of 40.05 Gy in 2.67 Gy single doses 5 weeks (+/- 2 week) after surgery when wound healing is completed. Patients treated in arm B will receive BCS followed by intermediate single-shot IOERT to the tumor cavity with a dose of 21 Gy prescribed to the 90%-isodose line.

Both groups will be evaluated after BCS at 5 weeks after treatment start (Study Visit 1), to assess to potential influence of IORT on fatigue (secondary endpoint). In group A this time point corresponds to 5 weeks after BCS, just before the start of RT; in group B this corresponds to 5 weeks after BCS incl. IORT.

After the first study visit patients will receive regular follow-up visits based on the standard follow-up program of current German guidelines. The second, third, fourth and fifth study visits are planned 12 weeks (primary endpoint), 6 months, 2 and 5 years (secondary endpoints) after the treatment start. These visits will include a clinical assessment as well as analysis of quality of life including fatigue (EORTC and Fatigue Assessment Questionnaires, BREAST-Q and BCTOS, see below for details). Photographic assessment of cosmetic results is also planned except for the last visit after 5 years. The last subject in (LSI) will be followed 5 years after baseline. This is considered the final study visit.

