#### -Study Visit (T2), primary endpoint

The second study visit is planned 12 weeks (+/- 2 week) after treatment start for both groups. For group A, this is 7 weeks after hypofractionated WBI, while for group B this visit is 12 weeks after IORT.

The following examinations will be performed:

- Clinical assessment using CRF
- Quality of life using the EORTC QLQ-C30, BREAST-Q and BCTOS
- Fatigue assessment using the Fatigue Assessment Questionnaire (FACIT Fatigue Scale)
- Photographic documentation for cosmetic assessment
- Assessment of adverse events

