| Documentation of AEs                              |                                       | X                       | X                        |                          |                         |                         |
| Photographic documentation of cosmetic assessment | X                                     | X                       | X                        |                          | X                       |                         |
| CRF Form                                          | X                                     | X                       | X                        | X                        | X                       | X                       |

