## Toxicity/ quality of life

Detailed acute and chronic potentially therapy-related toxicity will be assessed during each follow-up visit and documentation of side-effects with Common Terminology Criteria for Adverse Events and with the Radiation Therapy Oncology Group (RTOG)/ European Organization for Research and Treatment of Cancer (EORTC) Late Radiation Morbidity Scoring System Schema. Documentation of toxicity will mainly focus on breast shrinkage/distortion, breast induration/fibrosis, change of skin appearance, telangiectasia, breast oedema, numbness, fat necrosis and local pain. QoL will be analyzed with the help of the validated 30-item self-assessment questionnaire of the European Organization for Research and Treatment of Cancer (EORTC QLQ-C30, version 3.0). It is composed of five multi-item functional scales (physical, role, emotional, cognitive, and social function), three multi-item symptom scales (fatigue, pain, nausea/vomiting) combined with a global health and quality-of life scale. The other six single items assess further symptoms (dyspnea, insomnia, appetite loss, constipation, diarrhea) that are often reported by cancer patients as well as financial difficulties. Scores are interpreted according to the guidelines of the EORTC Scoring Manual.

The BREAST-Q questionnaire is a validated survey instrument especially developed for patients undergoing breast surgery. An extra BREAST-Q BCS module exists, which is specifically designed for patients undergoing BCS measuring quality-of-life (QOL) and satisfaction. Both of these topics are divided into three subscales i.e., QOL: physical, psychosocial and sexual well-being; Satisfaction: satisfaction with cosmetic outcome (breast appearance), satisfaction with overall outcome and satisfaction with care. Patients are asked to rate each item question on a four-point scale. The BREAST-Q is separated into a pre- and post-surgery version.

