### **9.1 Adverse Events**

Toxicity associated to irradiation that occurs for the first time after treatment start or preexisting toxicity that significantly increases in the severity grade after the start of study treatment likely to be related to radiotherapy will be documented within the subject's medical records and eCRF. Treatment related side effects will be recorded according to CTCAE v5.0 (Common Terminology Criteria for Adverse Events version 5.0; <http://www.eortc.be/services/doc/ctc>). Grades refer to the severity of the adverse event.

Acute toxicities are defined by the occurrence within the first 90 days after the start of RT. Adverse Events occurring after the first 90 days until 6 months after study treatment will be documented as subacute toxicities. Any adverse event emerging more than 6 months after RT will be recorded as late toxicities.

Standardized informed consent forms for irradiation of breast cancers are utilized to inform the patient about study treatment. Expected acute side effects of RT include radiation dermatitis, fatigue, pain, soreness and dryness of the breast, pruritus of the skin, hairloss in the axilla, sore

throat and change in breast size, shape and color. Characteristics and severity of subacute/ late side effects depend on the location and the extent of the target volume/ irradiation field and include skin fibrosis, change in breast size, shape and color, lymphoedema, lung fibrosis, rib fractures, cardiac disorders like cardiac arrhythmia, cardiac insufficiency and coronary heart disease, soft tissue necrosis as well as brachial plexopathy.

Acute/ subacute toxicities will be assessed prior, during and after RT, including:

- Skin disorders: radiation dermatitis, dryness and pruritus of the skin, hairloss in the axilla, lymphedema
- Breast disorders: pain, swelling, change in breast size, shape and color
- Endocrine disorders: hot flashes, night sweats, bone pain
- Lung disorders: coughing, dyspnea
- Gastrointestinal disorders: nausea and vomiting
- Other disorders: alopecia, weight loss

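### The visit schedule records adverse events only at 5 and 12 weeks and has no cosmesis instrument at 5 years, contradicting the toxicity and cosmesis time points set elsewhere in the protocol

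*Protocol*

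**What the plan says.** **Toxicity.** Section 2.2 sets five time points: "acute and chronic toxicity after 5 weeks, 12 weeks, 6 months, 2 years, 5 years after treatment start". Section 7.1.2 (Toxicity/quality of life) says that "potentially therapy-related toxicity will be assessed during each follow-up visit", using CTCAE and the RTOG/EORTC late morbidity scheme. Section 9.1 adds: "Any adverse event emerging more than 6 months after RT will be recorded as late toxicities".

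The operational parts of section 6.4 differ. The lists for T1 (5 weeks) and T2 (12 weeks) carry the item "Assessment of adverse events"; those for T3 (6 months), T4 (2 years) and T5 (5 years) do not. In the work-flow table the row "Documentation of AEs" is ticked at T1 and T2 only.

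**Cosmesis.** Section 2.2 sets "cosmesis 5 weeks, 12 weeks, 2 years, 5 years after treatment start". The narrative of 6.4 states: "Photographic assessment of cosmetic results is also planned except for the last visit after 5 years". In the table the row "Photographic documentation of cosmetic assessment" is ticked at baseline, T1, T2 and T4, and the BREAST-Q/BCTOS row is ticked at the same four visits. The T5 list contains only the CRF clinical assessment, the EORTC QLQ-C30 and the FACIT Fatigue Scale. Yet the same narrative names BREAST-Q and BCTOS among the questionnaires for the second to fifth visits.

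**The concern.** A visit schedule is what staff normally work from. Here two operational sources, the lists and the table, agree in leaving adverse events out at 6 months, 2 years and 5 years, so a single missed tick is an unlikely explanation. If they are followed, late events are recorded only when someone happens to raise them. How often that happens may differ by arm, since patients and staff know the treatment.

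Section 10.2.3 plans to tabulate adverse events and compare the arms by chi-squared test. That comparison means little unless events are sought in the same way in both arms. Section 7.1.2 directs attention to changes such as fibrosis, shrinkage, telangiectasia and fat necrosis, and section 1.1 cites an earlier electron-IORT trial with less skin toxicity and pulmonary fibrosis but more fat necrosis. Section 1.3 expects an advantage in chronic as well as acute toxicity. A late examination that was not made cannot be reconstructed afterwards. For 5-year cosmesis, the schedule leaves the objective with no measurement.

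**Working it through.** There is no sample-size or power figure to reproduce. The check sets the objectives against the schedule and then places the visits in the time windows of section 9.1.

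**Step 1: objectives against schedule.**

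| Visit | Toxicity objective (2.2) | AE item (list and table, 6.4) | Cosmesis objective (2.2) | Photograph (list and table) | BREAST-Q/BCTOS (list and table) | BREAST-Q/BCTOS (6.4 narrative, visits 2 to 5) |
|---|---|---|---|---|---|---|
| T1, 5 weeks | yes | yes | yes | yes | yes | not covered by that sentence |
| T2, 12 weeks | yes | yes | yes | yes | yes | yes |
| T3, 6 months | yes | **no** | no | no | **no** | **yes** |
| T4, 2 years | yes | **no** | yes | yes | yes | yes |
| T5, 5 years | yes | **no** | yes | **no** | **no** | **yes** |

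- Toxicity: 5 time points − 2 with an AE entry = 3 without (T3, T4, T5).
- Cosmesis: 4 time points − 3 with an instrument = 1 without (T5).
- BREAST-Q/BCTOS: narrative and schedule disagree at T3 and T5.

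**Step 2: which visits fall in the late window.** Section 9.1 defines acute as within 90 days of the start of RT, and late as more than 6 months after RT. Section 6.4 starts WBI (arm A) 5 ± 2 weeks after surgery, that is day 35 (21 to 49). IORT (arm B) is given at surgery, day 0. Nominal visit days are T1 = 5 × 7 = 35, T2 = 12 × 7 = 84 and T3 = 182, taking 6 months as 26 weeks.

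- T2 in arm A: 84 − 35 = 49 days after RT start (84 − 49 = 35 to 84 − 21 = 63). In arm B: 84 days.
- End of the acute window in arm A: 35 + 90 = day 125 (111 to 139). T2 is at day 98 at the latest (84 + 14), so the last scheduled AE entry precedes the end of the acute window in arm A. The two arms are also observed for different lengths of time since RT.
- T3 in arm A: at most 182 + 14 − 21 = 175 days after RT start. This is below 182, so T3 is subacute, not late. In arm B, T3 falls at 182 ± 14 = 168 to 196 days and straddles the boundary.
- T4 in arm A: nominally 730 − 49 = 681 to 730 − 21 = 709 days after RT start. T4 and T5 are late in both arms.

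No scheduled AE entry (T1, T2) lies in the late window in either arm.

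**Step 3: can the CRF assessment stand in?** The T1 and T2 lists name the CRF clinical assessment and the adverse-event assessment as separate items, and the table has separate rows for the two. A reader of the schedule would therefore take the CRF assessment at T3 to T5 not to include adverse events.

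**The case against.** The strongest reply is that the protocol does order late toxicity to be collected. Section 7.1.2 requires it at every follow-up visit, section 5.6 requires new or worsening abnormalities to go into the CRF, section 9.1 sends toxicity to the medical records and eCRF, and section 11.2 has side effects at follow-up monitored. A CRF clinical assessment remains at T3, T4 and T5. This stands. A reader might infer that the chronic-toxicity objective cannot be answered, or that none of 202 × 3 = 606 late visits will yield data. The documents do not support that: zero capture is the worst case, the eCRF is not shown, and T3 is not a late visit in arm A.

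A second reply is that the table is not exhaustive: it has no row for recurrence, survival or secondary malignancies, which are plainly to be collected. That is true, but those items have no row at all. Adverse events have a row that is ticked at some visits and left blank at others, and a blank there reads as an instruction.

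On cosmesis, leaving out the 5-year photograph looks deliberate, since narrative and table agree. The 6.4 narrative would supply BREAST-Q and BCTOS at 5 years, and section 7.1.2 gives both an aesthetic component. So it would also go too far to say that none of the 202 women will have 5-year cosmesis data. There is a further caution. Reference 68, on validating cosmetic assessment, and the breast-retraction abbreviations are not used in the text available, so a description of cosmesis methods may not have come through. That limits what can be said about the methods, but not about the T5 list and table, which are explicit.

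**Conclusion.** The point holds as an internal contradiction. The visit lists and work-flow table conflict with sections 2.2, 7.1.2 and 9.1 on toxicity, with section 2.2 on 5-year cosmesis, and with the narrative of 6.4 on BREAST-Q and BCTOS at T3 and T5. If the schedule is followed, 3 of 5 toxicity time points have no scheduled AE entry, the visits that are late in both arms (T4 and T5) have none, and 1 of 4 cosmesis time points has no instrument. The consequence is a risk of unsystematic late capture that is not comparable between arms, not certain loss of data.

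The size rests on staff following the lists and table rather than the text, and on 6 months taken as 182 days. The affected endpoints are secondary and analysed descriptively, and the primary endpoint at T2 is untouched. This should be fixed, but it does not threaten the main result.

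**What to change.** 1. Add adverse-event and late-toxicity documentation, with the CTCAE and RTOG/EORTC late scheme already named in 7.1.2, to the T3, T4 and T5 visit lists, and tick the table row at those visits.
2. For 5-year cosmesis, either add BREAST-Q and BCTOS at T5, as the 6.4 narrative already implies, or delete 5 years from the cosmesis objective in 2.2.
3. Make the 6.4 narrative and the table agree on BREAST-Q and BCTOS at T3 and T5.
4. Check that the eCRF pages for T3 to T5 match the result.

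The cost is an amendment to the text, table and eCRF. The visits already take place with a clinical assessment, so the burden is a little extra recording at each, plus two questionnaires at T5 if that option is taken. The roughly 30 extra minutes per visit in section 6.4 do not expressly include adverse-event recording, so that estimate may need a small revision.

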### **2.3 Explorative Objectives**

Gene expression analysis using the Prosigna/PAM50-assay to evaluate the potential prognostic/predictive impact on choice of radiotherapy modality

### **3. Trial Design**

This trial will be conducted as a prospective, randomized, two-arm Phase II study.

### **4. Trial Duration**

The overall duration of the trial is expected to be approximately 84 months. Recruitment of patients will start in January 2019. Recruitment of the patients is planned over a time period of 24 months, minimum duration of the follow-up phase will be 5 years.

Total trial duration: 84 months

Recruitment phase: 24 months

FSI (First Subject In): January 2019

LSI (Last Subject In): January 2021

LSO (Last Subject Out) – Primary Endpoint: April 2021

LSO (Last Subject Out) – Secondary Endpoints: January 2026

### **5. Selection of Patients**

#### **5.1 Number of Patients**

202 patients will be enrolled in this phase II clinical trial.

#### **5.2 General Criteria for Patients' Selection**

Women with early stage, low risk breast cancer eligible for breast-conserving surgery will be evaluated and screened based on the protocol. All patients fulfilling the inclusion and exclusion criteria will be informed about the possibility to participate in the study. Registration for the study must be performed prior to beginning of RT.

#### **5.3 Inclusion Criteria**

Women with early stage, low risk breast cancer eligible for breast-conserving surgery meeting all of the following criteria will be considered for admission to the trial:

- Histologically confirmed invasive breast cancer
- Total tumor size < 2.5 cm
- cNo
- estrogen receptor positive, HER2-negative on immunohistochemistry
- age  $\geq$  50 years
- ECOG Performance status  $\leq$  2

- Ability of subject to understand character and individual consequences of the clinical trial
- Written informed consent (must be available before enrolment in the trial)

## **5.4 Exclusion Criteria**

Patients presenting with any of the following criteria will not be included in the trial:

- G3
- Extensive microcalcifications
- Invasive lobular carcinoma
- Clinically involved lymph nodes
- No invasive axillary lymph node staging planned
- Patients with significant mental or physical comorbidities that preclude regular follow-up
- Neoadjuvant chemotherapy or neoadjuvant endocrine therapy
- previous radiotherapy of the breast
- Known carcinoma < 5 years ago (excluding Carcinoma in situ of the cervix, basal cell carcinoma, squamous cell carcinoma of the skin) requiring immediate treatment interfering with study therapy
- Pregnant or lactating women
- Participation in another competing clinical study or observation period of competing trials

## **5.5 Criteria for Withdrawal**

### **5.5.1 Withdrawal of Patients**

A subject may voluntarily discontinue participation in this study at any time at their own request or at request of the legal representative. In addition, study treatment will be discontinued if unmanageable toxicity is documented, or if the Principal Investigator makes a decision to terminate the study. A subject will be withdrawn from the protocol if, in the investigator's opinion, continuation of the trial would be detrimental to the subject's well-being. If the subject withdraws from the trial and also withdraws consent for disclosure of future information, no further evaluations should be performed, and no additional data should be collected. The PI may retain and continue to use any data collected before such withdrawal of consent, in case the patient has not withdrawn the further use of his data as well.

### **5.5.2 Handling of Withdrawals**

In all cases, the reason for withdrawal must be recorded in the Case Report Form and in the subject's medical records. In case of withdrawal of a subject at his/ her own request, the reason can be asked and documented. All efforts will be made to follow up the subjects and, all

examinations scheduled for the final trial day will be performed as far as possible on all patients and documented. All ongoing Adverse Events (AEs)/ Serious Adverse Events (SAEs) of withdrawn patients have to be followed up until no more signs and symptoms are verifiable or the subject is on stable condition.

#### **5.5.3 Replacement of Patients**

Patients will not be replaced if consent is withdrawn retrospectively and patients have already been randomized.

#### **5.5.4 Premature withdrawal of patients from the study**

Individual termination criteria during the treatment phase:

- at any time at the request of the patient
- occurrence of therapy-resistant severe side effects (CTC grade 4 toxicity, which does not recover spontaneously, after supportive therapy or after a radiation break)
- intraoperative re-classification of patient into non-low risk breast cancer, e.g. detection of positive sentinel lymph node
- R1/2 resection of the tumor

In the case of lymph node metastasis identified postoperatively, additional radiotherapy to the regional lymphatic basins should be considered. If a R1/2 resection status is diagnosed postoperatively, re-resection and additional whole-breast irradiation should be taken into account.

Individual termination criteria during the follow-up phase:

- at any time at the request of the patient

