The ultimate form of APBI is single-dose intraoperative radiotherapy (IORT) delivered to the tumor bed during BCS. Two large RCTs employing different techniques of IORT have been published so far: the ELIOT and the TARGIT-A-trial. The ELIOT-trial is a single-center RCT comparing one dose of 21 Gy of electron-IORT (IOERT) to WBI with 50 Gy and a tumor bed boost over 6 weeks. Inclusion criteria were non-restrictive resulting in inclusion of a considerable number of patients with risk factors such as tumor size > 2 cm, positive nodes, G3 as well as negative immunohistochemistry for ER and/or PR^26. 5-year results showed a local recurrence rate of 4.4% for patients receiving IORT and 0.4% for patients receiving WBI which was statistically significant, but below the pre-specified non-inferiority margin. However, when excluding patients with risk factors in the IORT-arm, the 5-year local recurrence rate was only 1.5%. Patients receiving IORT had significantly lower rates of skin toxicity and pulmonary fibrosis, but higher rates of fat necrosis.

The TARGIT-A trial is a multi-center RCT randomizing 3,451 patients to single-shot 20 Gy of 50 kV-IORT vs. 50 Gy of WBI in 25 fractions. In the IORT-arm, additional WBI was permitted in the case of risk factors and was delivered in 15.2% of patients in the IORT-arm^35. Furthermore, inclusion of patients who received IORT during a second operative procedure was allowed (post-pathology stratum). 5-year results were published in 2014, although only 1222 patients had a median follow up of 5 years. The median follow-up of the total cohort was 2 years and 5 months. The 5-year local recurrence rate was 3.3% in the IORT-arm and 1.3% in the WBI-arm ( $p = \text{n.s.}$ ). Non-inferiority was demonstrated for the pre-pathology stratum, but not for the post-pathology stratum. There were significantly less non-breast cancer-related deaths in the IORT-arm, although the reason was unclear.

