## 10. Statistical Considerations

### 10.1 Sample Size Calculation

The sample size calculation is based on the primary endpoint change of fatigue from baseline to week 12 after Treatment start (study visit T2 ) between the groups APBI and WBI measured via the FACT-Fatigue score. An improvement in 6 of 13 items by one point is considered clinically relevant resulting in a clinically relevant effect size of 6 points. Assuming a standard deviation of 12 and with a type I error rate of  $\alpha = 0.05$  (two-sided), a two sample t-test requires a total sample size of n=172 patients (86 per group) to achieve a power of  $1 - \beta = 0.90$  for revealing an effect of 6 points. Adjusting for the covariates baseline fatigue, age, and tumor size in a linear model is assumed to yield less unexplained variance and thus to an additionally increased power. Taking a dropout rate of 15% percent into account, n=202 patients need to be randomized. Sample size calculation was carried out using ADDPLAN v 6.1.

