#### 10.2.2 Confirmatory analysis

The null hypothesis to be tested states that the change in the FACT-F score between baseline and week 12 after treatment start is equal for both groups:

$$H_0 : \mu_{APBI} = \mu_{WBI}$$

This hypothesis will be tested at a two-sided level of significance of  $\alpha = 0.05$  against the alternative hypothesis:

$$H_1 : \mu_{APBI} \neq \mu_{WBI}$$

The hypothesis test will be conducted using a linear model with the dependent variable “change in FACT-F score between baseline and week 12 after treatment start” and the independent factors treatment group (A/B), baseline FACT-F score, tumor size, and age. The effect estimate for the treatment group will be calculated alongside a 95% confidence interval.

The confirmatory analysis will be primarily based on the FAS which is consistent with the intention-to-treat (ITT) principle by including all patients who were randomized to the two groups.

Missing data for the primary outcome variable will be replaced using multiple imputation taking the covariates treatment group, baseline FACT-F score, tumor size, and age into account by application of the fully conditional specification method. This will be realized using the option “FCS” of the SAS “MI” procedure which is implemented in SAS 9.4. M=10 imputations will be done and the regression approach will be used to impute the data.

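### Two findings at surgery end study participation after randomisation, the week-12 FACIT is then not secured, and imputation would treat these women as uncomplicated completers of their arm

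*Protocol*

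**What the plan says.** **Timing.** Section 6.4 puts the baseline visit 1 to 7 days before surgery. Arm B is irradiated during surgery, so allocation has to precede it. Anything learned at or after the operation is post-randomisation information.

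**Termination.** Section 5.5.4 is headed as premature withdrawal from the study. Its treatment-phase list includes "intraoperative re-classification of patient into non-low risk breast cancer, e.g. detection of positive sentinel lymph node" and "R1/2 resection of the tumor". The first is limited to intraoperative findings; the second has no timing. The section then gives treatment advice for findings made postoperatively: regional nodal radiotherapy to be considered for nodal metastasis, re-resection and additional whole-breast irradiation (WBI) for R1/2. Nodal metastasis found only postoperatively is not on the termination list.

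**Follow-up after withdrawal.** Section 5.5.2 asks for every effort to follow withdrawn women and says that "examinations scheduled for the final trial day will be performed as far as possible on all patients and documented". It does not mention week 12.

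**Analysis.** Section 10.2.1 places every randomised woman in the full analysis set (FAS) by assigned arm, and section 10.2.2 states: "The confirmatory analysis will be primarily based on the FAS which is consistent with the intention-to-treat (ITT) principle". Only a missing primary outcome is imputed, using treatment group, baseline score, tumour size and age. The one sensitivity analysis named in section 10.2.3 is per-protocol (PP).

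**The concern.** Section 5.5.1 can tell stopping study treatment from leaving the protocol, since it uses separate sentences for the two. Section 5.5.4 does not make that distinction, so a site that follows its heading may stop collecting questionnaires from these women. The final-day wording in 5.5.2 does not rescue the primary endpoint. Section 6.4 calls the 5-year visit the final one, and if an exit visit is meant instead, it would fall soon after surgery. Neither is week 12.

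A score lost this way is not lost at random. The imputation model has no term for reason of withdrawal or radiotherapy received. An arm B woman who goes on to WBI would be filled in as if she had had IORT alone. WBI is the treatment that the protocol expects to be more fatiguing (sections 1.1 and 2). If it starts about five weeks after surgery, as section 6.2 describes for WBI, it begins before the week-12 assessment. The estimate then drifts from the effect of choosing IORT before surgery towards its effect when nothing further is needed.

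The PP analysis probably cannot reveal this. It is restricted to women treated as allocated without major deviations, so it is likely to leave the same women out. This matters because the trial has a single confirmatory test.

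**Working it through.** **1. The plan's own figure.** Section 10.1 gives a difference of 6, SD 12, two-sided 0.05 and power 0.90. The exact two-sample t-test needs 85.03 per arm, rounded up to 86, or 172 in total; power at 86 per arm is 0.903. With 15% dropout, 172/0.85 = 202.35, against the stated 202. The sample size reproduces.

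**2. Quantities the protocol does not give (all assumptions).**
- p: share of women meeting a listed criterion, equal in both arms; range 5% to 20%.
- f: share of those women without a week-12 score; 50% or 100%.
- h and g: how many points worse the affected women in arm B (h) and arm A (g) score than WBI completers; range 0 to 9. With h = 0, affected arm B women look like WBI completers.
- d: APBI minus WBI difference among unaffected completers, set to 6.

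**3. Formulas.** Scores run from 0 (worst) to 52 (best), so a positive difference favours APBI.
- Difference with every randomised woman's actual score: T = (1 - p)d + p(g - h).
- Difference when missing scores are filled from the observed scores of the same arm: M = [(1 - p)d + p(1 - f)(g - h)] / (1 - pf).
- Bias: M - T = pf(1 - p)(d + h - g) / (1 - pf). At f = 100% this is p(d + h - g); at f = 0 it is zero.

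**4. Equal added fatigue in both arms (h = g), d = 6.**

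| p | T | bias, f = 100% | bias, f = 50% |
|---|---|---|---|
| 5% | 5.7 | 0.30 | 0.15 |
| 10% | 5.4 | 0.60 | 0.28 |
| 15% | 5.1 | 0.90 | 0.41 |
| 20% | 4.8 | 1.20 | 0.53 |

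For example, at p = 15% and f = 50%: 0.15 × 0.5 × 0.85 × 6 / (1 - 0.075) = 0.41.

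**5. Unequal added fatigue, p = 15%, f = 100%.**
- g - h = 3: 0.15 × (6 - 3) = 0.45.
- g - h = 6: 0.15 × (6 - 6) = 0.
- g - h = 9: 0.15 × (6 - 9) = -0.45, against APBI.
- h - g = 3: 0.15 × (6 + 3) = 1.35.

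If completers do not differ (d = 0) and h = g, the bias is zero.

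**6. Simulation of the regression imputation.** Settings: 101 per arm, 10 imputations, 600 runs, treatment and baseline as predictors, all affected scores missing. Monte Carlo error is about 0.07.

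| p, d, h, g | imputed | all scores kept |
|---|---|---|
| 10%, 6, 0, 0 | 5.95 | 5.36 |
| 15%, 6, 0, 0 | 6.09 | 5.16 |
| 15%, 6, 3, 3 | 6.02 | 5.11 |
| 15%, 6, 0, 6 | 6.05 | 6.08 |
| 15%, 6, 0, 9 | 5.96 | 6.44 |
| 15%, 0, 3, 0 | 0.01 | -0.41 |

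These agree with the formulas within simulation error.

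**The case against.** The other side has several good points.

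- **The analysis set is ITT.** A reader might infer that the primary analysis is not ITT at all. The text does not support that: the FAS holds every randomised woman by assigned arm, and an observed week-12 score is used whatever else she received. The weakness lies in outcome collection and the missing-at-random assumption. This stands.
- **Nodes.** A reader might infer that every woman found node-positive at or after surgery is terminated. Only intraoperative re-classification is listed; nodes found later attract treatment advice. This stands.
- **Follow-up is requested.** Section 5.5.2 does not abandon withdrawn women, so a missing score is a risk, not a certainty. This stands, but the request does not reach the primary time point.
- **Both arms are affected.** Arm A women with these findings may have further surgery or nodal radiotherapy and would likewise be imputed as uncomplicated. The direction of bias is therefore not fixed, as step 5 shows.
- **Power.** A reader might take the background statement that in another trial "additional WBI was permitted in the case of risk factors and was delivered in 15.2% of patients in the IORT-arm", shrink the 6 points by that share and call the stated power too high. That figure comes from a multicentre 50 kV trial which also admitted IORT at a second operation; it is not a planning figure here. Section 10.1 sets 6 points as the clinically relevant difference between the randomised groups, not as a forecast among completers, so powering for it is no error.
- **The SAP.** Sensitivity analyses are often left to a SAP, which is not at hand. But no SAP can recover scores that were never collected, so the collection rule belongs in the protocol.

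**Conclusion.** The point holds as a gap between sections 5.5.2, 5.5.4 and 10.2.2. As written, two findings made after randomisation end study participation and the week-12 FACIT is not secured. Any resulting gap is filled on the assumption that the woman resembles completers of her own arm. ITT holds for the analysis set but is not secured for the outcome.

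Overstatement of APBI is plausible, and most easily seen after R1/2, where section 5.5.4 raises additional WBI: in arm B that is the comparator treatment, while arm A receives WBI anyway. For 5-20% of women affected, equal added fatigue in both arms and 50-100% of their scores missing, it is about 0.15 to 1.2 points against a target of 6. It is zero if all scores are collected, zero if the event adds 6 points more fatigue in arm A than in arm B, and reversed beyond that. None of these inputs is in the protocol, so a firm claim that the plan favours APBI is not supported.

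**What to change.** Reconcile 5.5.2 and 5.5.4 without changing any clinical criterion or treatment advice:

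1. State in 5.5.4 that meeting a listed criterion does not end data collection.
2. State in 5.5.2 that FACIT is collected at T2, and at the other scheduled visits, from every randomised woman unless she withdraws consent for it.
3. State outright in 10.2.2 what the FAS definition already implies: observed scores are analysed as randomised whatever further surgery or radiotherapy was given, and only truly missing scores are imputed.
4. Add a sensitivity analysis that does not assume these women resemble same-arm completers, for instance imputing arm B women who received WBI from arm A. This needs the radiotherapy actually received to be recorded alongside the withdrawal reason that 5.5.2 already requires.

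The cost is a short amendment and a few more questionnaires; section 7.1.1 puts FACIT at 5 to 10 minutes. The estimated effect may come out somewhat smaller. No change to the sample size or restatement of power is required.
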